## 6.3 Duration of Treatment for Each Patient at Each Cohort

Six months of treatment is recommended for patients who have a response, unless or until:

- Patients exhibit progression of disease together with worsening of biliary function, no longer meeting eligibility criteria, or exhibiting symptomatic progression; or patients exhibit progression of disease which was confirmed after 2 additional treatment cycles

- Unacceptable toxicity from CPI-613

- Patient withdrawal of consent

- Investigator’s discretion to withdraw patients from the study because continued participation in the study is not in the patient’s best interest.

- Undercurrent illness: a condition, injury, or disease unrelated to the intended disease for which the study is investigating, that renders continuing the treatment unsafe or regular follow-up impossible

- General or specific changes in the patient's condition that renders the patient ineligible for further investigational treatment

- Non-compliance with investigational treatment, protocol-required evaluations or follow-up visits

- Termination of the clinical trial by the sponsor

However, if therapy is considered beneficial according to the opinion of the treating physician, additional cycles of therapy may be given on the same treatment plan indefinitely up to the time of clear disease progression.

When terminating treatment during this trial, the investigator should make every effort to contact the patient and to perform a final evaluation. Also, the reason(s) for withdrawal from the study must be recorded.

Survival and post-study cancer treatment will be monitored via bi-monthly telephone contact once patients are removed from trial. All patients will be followed until death.

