**Primary objective**

To evaluate the safety and anti-cancer activities (assessed based on Response Rate) of CPI-613 in patients with advanced unresectable bile duct cancer who have failed available therapies.

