**Design**

Open-label single arm

* Maximum number of cycles allowed is 6

** Two additional cycles will not be given if the patient no longer meets eligibility criteria, has worsening of biliary function, or has symptomatic progression.

Table of Contents

[SCHEMA 3](#_Toc363723897)

[1.0 BACKGROUND AND STUDY OBJECTIVES 6](#_Toc363723898)

[1.1 Small Cell Lung Carcinoma 6](#_Toc363723899)

[1.2 CPI-613 6](#_Toc363723900)

[2.0 STUDY DESIGN 7](#_Toc363723901)

[2.1 Study Objective 7](#_Toc363723902)

[2.2 Outcome Measures 7](#_Toc363723903)

[2.3 Open-Label, Single-Arm Study Design 7](#_Toc363723904)

[3.0 PATIENT ELIGIBILITY CRITERIA 8](#_Toc363723905)

[3.1 Inclusion Criteria 8](#_Toc363723906)

[3.2 Exclusion Criteria 8](#_Toc363723907)

[3.3 Inclusion of Women and Minorities 9](#_Toc363723908)

[4.0 REGISTRATION PROCEDURES 9](#_Toc363723909)

[5.0 STUDY PROCEDURES 11](#_Toc363723910)

[5.1 Pre-Study Screening Tests and Safety Assessment 12](#_Toc363723911)

[5.1.1 Pre-Study Screening Tests 12](#_Toc363723912)

[5.1.2 Safety Assessment 12](#_Toc363723913)

[5.1.3 Tumor Assessment 12](#_Toc363723914)

[5.2 Specifics of Tests Performed During the Study 13](#_Toc363723915)

[5.2.1 ECOG Performance Status 13](#_Toc363723916)

[5.2.2 Clinical Chemistry and Hematology 14](#_Toc363723917)

[6.0 TREATMENT WITH CPI-613 14](#_Toc363723918)

[6.1 Sample Size, Dose Levels and Justification of the Dose 15](#_Toc363723919)

[6.2 Adverse Event-Related Dosing Delay and Dose Modification 15](#_Toc363723920)

[6.3 Duration of Treatment for Each Patient at Each Cohort 16](#_Toc363723921)

[7.0 STUDY DRUG - CPI-613 17](#_Toc363723922)

[7.1 Description of CPI-613 Drug Product 17](#_Toc363723923)

[7.2 Handling of CPI-613 17](#_Toc363723924)

[7.3 Storage of CPI-613 17](#_Toc363723925)

[7.4 Intravenous (IV) Infusion Sets, Syringes and IV Bags to be used for Administration of CPI-613 17](#_Toc363723926)

[7.5 Reconstitution and Administration of CPI-613 18](#_Toc363723927)

[7.6 Request for CPI-613 19](#_Toc363723928)

[7.7 Procurement of Investigational Drug 20](#_Toc363723929)

[7.8 Disposal of CPI-613 20](#_Toc363723930)

[7.9 Calculation of the Amount of CPI-613 for Each Patient 21](#_Toc363723931)

[7.10 Concomitant Medications and Prophylactic Treatment 21](#_Toc363723932)

[8.0 ADVERSE EVENTS LIST AND REPORTING REQUIREMENTS 22](#_Toc363723933)

[8.1 Adverse Event Characteristics 22](#_Toc363723934)

[8.2 STRC SAE Reporting Requirements 23](#_Toc363723935)

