### 5.1.3 Tumor Assessment

Tumor response will be assessed based on RR, and PFS, derived from contrast CT of chest and abdomen and/or PET/CT at baseline and after every two cycles. Contrast CT and/or PET/CT should be performed during week 4, preferably on Wednesday or later (days 3, 4 or 5). RR is the primary endpoint, whereas PFS and OS are secondary endpoints.

According to the Response Evaluation Criteria in Solid Tumors (RECIST), the efficacy of treatment for solid tumors is determined by the tumor size. RECIST criteria are the golden standard to evaluate the tumor. In this study RECIST criteria will be used to evaluate response. However, there is a *pseudoprogression* phenomenon described with the use of CPI-613 in Phase I solid tumor studies (Lee et al. 2012).

It is felt that if CPI-613-induces necrosis of the tumor lesion there may be some radiographic evidence for increasing size. CPI-613 induces tumor necrosis due to its mechanism of action – selectively targeting the altered form of mitochondrial energy metabolism in tumor cells, causing changes in mitochondrial enzyme activities and redox status, which leads to apoptosis, necrosis, and autophagy of tumor cells (Lee et al., 2011; Lee et al., 2012; Senzer et al., 2012; Zachar et al., 2011; Retter et al., 2012).

For the purposes of this study, pseudoprogression will be defined and considered in patients who meet RECIST criteria of progression. It will be the treating physician’s discretion to continue treatment in this situation if the patience is deemed to be getting clinical palliative benefit. In these patients, the study drug can be given for another two cycles prior to making definitive determination of progression or response.

OS will be determined from the first dose of CPI-613 to death, assessed until patient death..Post-study survival, medical and cancer treatment information will be collected bimonthly via telephone contact after treatment termination.

RR is defined as % of patients who experienced a complete response (CR) or partial response (PR). CR and PR are based on Response Evaluation Criteria in Solid Tumor (RECIST) Version 1.1 (Eisenhauer et al. 2009). The best response recorded from the start of the treatment until disease progression (DP) will be considered.

PFS will be determined from the first dose of CPI-613 to DP or death due to any cause.

*5.1.4 Use of pre-study data for analyses*

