# 6.0 TREATMENT WITH CPI-613

CPI-613 will be administered to patients as shown in Table 6-1 (below). A treatment cycle is 4 weeks, with CPI-613 given on Days 1 and 4 of the first 3 weeks (i.e., 3-weeks-on-1-week-off). During each treatment cycle, patients will be treated with CPI-613 at the same dose, unless dose modification is warranted (see Section 6.2).

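### The 6-cycle maximum conflicts with open-ended treatment elsewhere, and the rules for treating past progression disagree and carry a criterion from a bile-duct-cancer study

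*Protocol*

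**What the plan says.** **Duration.** In the Protocol's front summary, a footnote under Design reads "Maximum number of cycles allowed is 6". Section 6.0 defines the unit: "A treatment cycle is 4 weeks, with CPI-613 given on Days 1 and 4 of the first 3 weeks". Four other places set no cap:

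- The schema keeps patients with response, stable disease or clinical benefit on treatment until progression is clear.
- Table 5-1, footnote f, schedules on-treatment imaging in cycles 2, 4 and 6 and then at two-cycle intervals up to progression.
- Table 6-1 writes out cycles 1 and 2 and then carries on to progression.
- Section 6.3 opens with "Six months of treatment is recommended for patients who have a response", subject to a list of stopping reasons. It closes by saying that, where the treating physician sees benefit, "additional cycles of therapy may be given on the same treatment plan indefinitely up to the time of clear disease progression".

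**Treatment at and after progression.** The first stopping reason in section 6.3 is "Patients exhibit progression of disease together with worsening of biliary function, no longer meeting eligibility criteria, or exhibiting symptomatic progression". The other half of that bullet is progression confirmed after two more cycles. A second Design footnote refuses the two additional cycles on the same three grounds. Section 5.1.3, on pseudoprogression in patients who meet RECIST progression, says "It will be the treating physician’s discretion to continue treatment in this situation", provided the patient is judged to have palliative benefit. It allows two more cycles before progression or response is finally determined, and mentions none of the three grounds.

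**Bile-duct text.** After the SCLC objectives, the front summary carries another primary objective, for "patients with advanced unresectable bile duct cancer who have failed available therapies".

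**The concern.** A fixed maximum and an open-ended rule cannot both govern the same patient. The rules for the two cycles after progression also differ between sections, and one of their conditions has no defined meaning in an SCLC trial.

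This is more than a clerical matter. The rules decide how much drug a patient may receive. They also decide who is treated past RECIST progression while the final call of progression or response is pending. Section 5.1.3 counts the best response up to progression and ends PFS at progression or death, so the primary endpoint and a secondary endpoint both depend on how the post-progression rule is applied. The duration rule also decides how long scheduled scans continue.

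**Working it through.** The plan gives no computed figure on this point to reproduce. The check is a comparison of sections plus unit conversion.

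**Inputs.** Cap of 6 cycles (Design footnote); 4-week cycle with 6 infusions (section 6.0); two additional cycles (Design footnote, 5.1.3, 6.3); 20 patients and PFS rates at 6 months and 1 year (section 9.0); median survival of 4 to 5 months after relapse (section 1.1). Assumed conversion: 1 month = 30.4375 days.

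**Step 1: cap against open-ended treatment.**
- Cap: 6 × 4 = 24 weeks, or 24 × 7 / 30.4375 = 5.5 months; 6 × 6 = 36 infusions.
- First progression on the cycle 6 scan plus two cycles: 6 + 2 = 8 cycles = 32 weeks, beyond the cap.
- Appendix D prints visits to cycle 10 (40 weeks, 9.2 months). These are form fields, not a rule, but they fit the open-ended reading.

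**Step 2: six months against the cap.** 6 × 30.4375 / 7 = 26.1 weeks, and 26.1 / 4 = 6.5 cycles. The two differ by about half a cycle, so the firm conflict is between the cap and the open-ended rule.

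**Step 3: the progression rules side by side.**

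| Patient with RECIST progression | Design footnote | Section 6.3, progression bullet | Section 5.1.3 |
|---|---|---|---|
| Symptomatic, judged to have palliative benefit | Two cycles refused | Ends treatment | Two cycles allowed |
| No symptoms, still eligible, no judged benefit | Two cycles not refused | Not met until progression is confirmed after two more cycles | No support for continuing |

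The sections give different answers for both patients. On the biliary ground, total bilirubin and alkaline phosphatase are on the chemistry panel (section 5.2.2), but nothing says which test or what change counts as worsening. Appendix F has a single box for progression, so the form need not show which rule was applied.

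**Step 4: size for the endpoints.**
- Response rate: one patient whose classification depends on the two cycles is 1/20 = 5 percentage points.
- PFS: 2 × 4 = 8 weeks, if the date is taken after the additional cycles and not at first RECIST progression. Median survival of 4 to 5 months is 17.4 to 21.7 weeks, so 8 weeks is 8/21.7 = 37% to 8/17.4 = 46% of it.

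**Step 5: imaging.** Under the cap, on-treatment scans fall in weeks 8, 16 and 24. The PFS landmarks are at 26.1 and 52.2 weeks. The follow-up column of Table 5-1 lists only telephone contact, and the Appendix E call form asks about survival and later treatment but has no progression item. A patient still progression-free in week 24 therefore has no further scheduled scan under the cap. Under the open-ended rule, scans continue in week 32 and beyond.

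**The case against.** The strongest reply is that one footnote stands against the operative text. Four places allow treatment to progression and only the Design footnote dissents. It follows a bile-duct objective and looks like residue from another protocol. That is plausible, but the footnote is current text. The biliary wording also stands in section 6.3 itself, so it cannot all be set aside as front-page residue.

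Second, section 5.1.3 can be read as discretion within the limits of section 6.3. That would work if 5.1.3 referred to those limits. It does not, and the two patients in the table get different answers.

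Third, the cap would bind for few. If the median survival of 4 to 5 months applies here, fewer than half of the 20 patients would be alive at 24 weeks, and the analysis is descriptive. This limits the effect of the cap. It does not limit the progression rule, which operates from the first scan in cycle 2.

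A reader might also draw stronger conclusions that the text does not support:

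- That there are three competing durations. Six months is only recommended, nearly equals 6 cycles, and is expressly extended within section 6.3.
- That stopping is undefined for SCLC. Biliary function is one of three alternatives. Symptomatic progression, loss of eligibility, toxicity, withdrawal of consent and investigator discretion all apply to these patients.
- That ending treatment before a PFS landmark spoils the estimate. PFS does not require continued treatment; the issue is the loss of scheduled imaging.
- That safety as an objective is only a bile-duct leftover. Section 2.1 states it for SCLC.

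**Conclusion.** The point holds in two parts. First, the 6-cycle maximum contradicts the schema, Tables 5-1 and 6-1 and section 6.3; permitted exposure is 24 weeks (36 infusions) on one reading and has no upper limit on the other. Second, the Design footnote and section 6.3 apply conditions to treatment after progression that section 5.1.3 does not carry, and one of them is an undefined biliary criterion taken over from another disease.

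The possible effect is 5 percentage points of response rate for each patient affected and up to 8 weeks on an individual PFS date. Under the cap, no scan is scheduled after week 24. The PFS figure assumes that progression is dated after the additional cycles. How many patients would be affected cannot be derived from the Protocol. The matter should be corrected, but it does not invalidate the design.

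**What to change.** The sponsor should reconcile the schema, the Design footnotes, Table 5-1 footnote f, section 5.1.3, Table 6-1 and section 6.3 into one duration rule and one rule for treatment after RECIST progression, stated once and cross-referenced. The bile-duct objective in the front summary, and the biliary wording in the Design footnote and section 6.3, should be resolved against the SCLC objectives. Which duration and which post-progression rule are right is a clinical decision for the sponsor, and this review takes no position on it.

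Once the rules are settled, check that Appendices D and F match them, and that the scans they schedule support the 6-month and 1-year PFS estimates in section 9.0.

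The reconciliation itself costs only amendment wording. It needs no change to the sample size or the analysis methods.

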# 7.0 STUDY DRUG - CPI-613

## 7.1 Description of CPI-613 Drug Product

CPI-613 is provided in 10-mL amber glass vials. Each vial contains 10 mL of CPI-613 at a concentration 50 mg/mL, equivalent to 500 mg of CPI-613. The drug product of CPI-613 is a clear and colorless solution that is free of any particulate matter.

## 7.2 Handling of CPI-613

CPI-613 is an investigational drug and its toxicity in humans is not fully understood. All necessary precautions in handling potentially toxic chemicals must be strictly adhered to. Gloves and protective clothing must be worn when handling CPI-613. Avoid contact by all modes of exposure. If the solution contacts the skin, it must be washed immediately and thoroughly with soap and water. If the solution comes in contact with mucous membranes, the membranes must be flushed thoroughly with water. Spills should be picked up with absorbent material and the area must be washed at least 3 times with ethyl alcohol followed by water.

CPI-613 drug product is slightly photosensitive (Study# PHO-001). Therefore, after removal of CPI-613 drug product from the amber vials, CPI-613 drug product should be protected from excessive light before administration to patients.

## 7.3 Storage of CPI-613

CPI-613 can be stored at room temperature and preferably stored under refrigeration, at 2˚-8˚C (36˚-46˚F), except when being prepared for administration.

## 7.4 Intravenous (IV) Infusion Sets, Syringes and IV Bags to be used for Administration of CPI-613

CPI-613 must be administered IV by infusion, via an IV catheter with D5W running at a rate of about 125-150 mL/hr. To avoid local reactions at and around the site of administration, CPI-613 should be administered via a central venous catheter. Subsequent sections describe the appropriate types of IV catheters, IV bags, syringes and clinical solutions that can be used in mixing and administering CPI-613 to patients.

Leaching of Diethylhexyl Phthalate (DEHP): CPI-613 can cause leaching of DEHP from IV infusion sets and IV bags (Study COM-003). Therefore, DEHP-containing IV infusion sets, IV bags or syringes should not be used in mixing or administration of CPI-613. Examples of the IV sets, IV bags and syringes that do not contains DEHP and therefore can be used in the administration of CPI-613 are:

**Extension Set for Syringe Pump Use: All extension sets from MED-RX do not contain DEHP.**

Syringes: A**ll Monoject syringes are DEHP free.**

IV Infusion Sets: A compatibility study has been conducted showing that CPI-613 is compatible with 4 commonly used IV infusion sets (Study# COM-001). Therefore, these 4 types of IV infusion sets, and IV infusion sets that are made with the same materials, can be used to administer CPI-613. These IV infusion sets are:

- PVC material - ADDitIV^®^ Primary IV Set with Universal Spike, Backcheck Valve, 2 Injection Sites, DEHP-Free and Latex-Free, 15 drops/mL, REF V14453, B Braun Medical Inc.
- Latex material - Interlink^®^ System Secondary Medication Set, 10 drops/mL, 2C7451, Baxter Healthcare Corporation
- PVC material - Surshield^TM^ Safety Winged Infusion Set, 0.19 mL Volume, Latex-Free, DEHP-Free, SV*S25BLS, Terumo Medical Products Hangzhou Co. Ltd.
- Polyethylene material - Interlink^®^ System Paclitaxel Set by Baxter HealthCare, Non DEHP-free:  Polyethylene tubing with a 0.22 microfilter Item # 2C7558 10 drops/mL

Syringes: Compatibility studies (Studies# COM-001 and COM-002) have shown that CPI-613 drug product (50 mg/mL), and drug product diluted with D5W to various concentrations (1.6-25 mg/mL) are compatible with various types of syringes, as listed below. Therefore, any of these types of syringes, and syringes that are made with the same materials, can be used to administer CPI-613. Also, glass syringes can also be used, since glass (such as glass containers) is compatible with CPI-613 drug product.

- Norm-Ject, polyethlyene barrel, polyethylene plunger, latex free (Henke Sass Wolf GMBH) syringes
- Becton Dickinson syringes
- Terumo syringes
- Monoject syringes
- Glass syringes

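### Section 7.4 rules out infusion sets containing DEHP, yet one of its four permitted sets (2C7558) carries a label that literally says it is not free of DEHP

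*Protocol*

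**What the plan says.** Section 7.4 of the protocol first names the hazard: "CPI-613 can cause leaching of DEHP from IV infusion sets and IV bags (Study COM-003"). It then draws the rule: "DEHP-containing IV infusion sets, IV bags or syringes should not be used in mixing or administration of CPI-613". The next sentence introduces examples of sets, bags and syringes as items without DEHP, usable for that reason.

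The infusion sets follow under their own paragraph, which gives compatibility as the ground for permission: "A compatibility study has been conducted showing that CPI-613 is compatible with 4 commonly used IV infusion sets (Study# COM-001"). It concludes that "these 4 types of IV infusion sets, and IV infusion sets that are made with the same materials, can be used to administer CPI-613". Four sets are named. The last is the "Interlink^®^ System Paclitaxel Set by Baxter HealthCare, Non DEHP-free", and the entry continues "Polyethylene tubing with a 0.22 microfilter Item # 2C7558 10 drops/mL".

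**The concern.** A permitted item carries the description that the same section gives as the reason not to use an item. Section 7.4 is the working instruction from which a pharmacist or nurse picks infusion equipment, and the hazard is one the protocol itself raises. Two careful readers could act in opposite ways. One takes the label at its word and excludes 2C7558 under the restriction. The other sees the set on the permitted list and uses it. If the label were literally true, the second reader would be following the protocol into the situation it means to prevent.

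**Working it through.** No arithmetic is involved beyond counting entries, and the protocol gives no figure to reproduce. The check sets the statements of Section 7.4 side by side and looks for anything elsewhere that settles them.

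1. **Rule.** Sets containing DEHP should not be used ("DEHP-containing IV infusion sets, IV bags or syringes should not be used in mixing or administration of CPI-613"). No exception is stated, for any material or for sets that passed a compatibility test.

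2. **Introduction to the examples.** The items are presented as not containing DEHP.

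3. **The four permitted infusion sets and their DEHP statements.**
   - PVC primary set V14453: labelled free of DEHP ("2 Injection Sites, DEHP-Free and Latex-Free").
   - Latex secondary set 2C7451: no DEHP statement ("Interlink^®^ System Secondary Medication Set, 10 drops/mL, 2C7451, Baxter Healthcare Corporation").
   - PVC winged set SV*S25BLS: labelled free of DEHP.
   - Polyethylene paclitaxel set 2C7558: "Interlink^®^ System Paclitaxel Set by Baxter HealthCare, Non DEHP-free".

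   The count is 2 labelled free + 1 silent + 1 labelled not free = 4. Only the last conflicts with steps 1 and 2. Silence on the latex set contradicts nothing.

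4. **Does the ground for permission resolve it?** The sets are permitted because of study COM-001. The reference list dates that study 2006 and titles it as compatibility testing of the drug product with infusion sets. The DEHP release study, COM-003, is dated 2009. As the protocol describes them, compatibility in COM-001 does not establish that a set is free of DEHP, so being on the list does not settle the label.

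5. **Does the context suggest what was meant?** Yes. The entry gives the material as polyethylene and repeats this for the tubing. The title of COM-003 in the reference list concerns PVC-containing sets and bags. The introduction in step 2 presents the examples as DEHP-free. All three point to an intended non-DEHP. None states the DEHP status of the whole set, because the entry describes only tubing and filter.

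6. **Is there a correction elsewhere?** Section 7.5 covers dilution and administration and does not mention DEHP. No other section comments on item 2C7558.

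**The case against.** The strongest reply is that this is a slip of the pen with no demonstrated consequence. The restriction governs. A reader who takes the label literally leaves the set out, which is safe. A reader who takes it as non-DEHP uses a polyethylene set that the section presents as DEHP-free. Harm requires that the set really contains DEHP, and only the manufacturer could show that. The items are offered as examples, and two other listed sets are clearly labelled free of DEHP, so no patient depends on this one.

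Most of this stands, and it is why the point is minor. It does not remove the error. The text as written contradicts itself on a named hazard, and the reader at the bedside cannot tell from the protocol which half is wrong. One could also argue that the DEHP-free introduction covers only the extension sets and syringes named directly after it, since the infusion sets have their own introduction. That narrower reading would weaken the evidence for a slip, but the conflict with the restriction would remain.

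Three stronger readings are tempting and are not supported:

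- *A reader might infer that the protocol directs patients to a DEHP-containing set, or that patients were exposed.* The protocol does not show that the set contains DEHP. It gives no leached amount and no resulting toxicity.
- *A reader might try to size the problem by the number of infusions in the trial.* The protocol does not say how often 2C7558 would be used. Treatment continues until progression, so a count over the first cycles is neither an exposure estimate nor an upper bound.
- *A reader might see further contradictions in the latex set without a DEHP statement, or in the permission for sets of the same materials, which include PVC.* The general restriction already covers both. They could be worded more clearly, but they do not conflict with anything.

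**Conclusion.** The point holds as a minor patient-safety wording error. One of four permitted infusion sets has a label that, read literally, contradicts the restriction in the same section and the introduction to its examples. It is probably a slip for non-DEHP, but that is an inference from context, which the protocol alone cannot confirm. The conclusion rests only on the printed text of Section 7.4 and on the absence of any correction elsewhere. It assumes nothing about the actual composition of the set. The response rate, PFS, OS, the sample size of 20 and the planned analyses are unaffected.

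**What to change.** Check the manufacturer's label for item 2C7558. If the set is free of DEHP, change the entry to say so in the form used for the two PVC sets. If it is not, or if this cannot be confirmed, delete the entry.

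The cost is one label check by the pharmacy or drug supplier and a change of a few words. The only downside is that the list may shrink from four sets to three.

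Two optional clarifications could be made at the same time: confirm the DEHP status of the latex set 2C7451, and add a DEHP-free condition to the permission for sets made of the same materials. Neither is needed to resolve the contradiction.
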